## Introduction

An acute moderate-to-severe lower respiratory tract infection (LRTI) or pneumonia in older adults is generally characterised by diagnostic uncertainty, a high risk of complications and negative outcomes, including mortality.^1 2^ Care in the home situation often acutely falls short because of increased dependency due to falls, decline in activities in daily living (ADL) or a state of confusion. This often leads to a presentation at the emergency department (ED) with the goal to define the optimal treatment plan which usually consists of a combination of antimicrobials, oxygen suppletion and/or inhalation medication, treatment and/or prevention of delirium, and additional help in ADL; and the optimal treatment location. Although, these treatments can be organised outside the hospital, for example, at home or in a nursing home, hospitalisation often occurs because of the 24/7 open access of EDs, and treatment outside the hospital is often considered irresponsible or impossible due to difficulties in ADL and the lack of (available) care.^3–6^

Such hospitalisations of older adults can be considered unnecessary or avoidable when they are related to poor transmural collaboration and different treatment protocols between regional care partners (general practitioners (GPs), hospitals, nursing homes and homecare institutions), the lack of diagnostic and treatment possibilities in primary care, the lack of (acute) availability and capacity in nursing homes and homecare, or the presence of financial barriers.^7–11^ Especially in older adults, hospitalisations are associated with iatrogenic harm such as delirium, falls and functional decline.^12–14^ As a consequence, older patients often show further decline in ADL from these hospitalisations, and as a result are often transferred to a nursing home or revalidation centre for further recovery. We hypothesise that these hospitalisations may be avoided when the care is well coordinated between care partners.

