### Outcomes

The primary outcome is the feasibility of the care pathway, which is defined as the percentage of patients treated outside the hospital, according to the care pathway, whom fully complete their treatment without the need for hospitalisation within 30 days of follow-up. This will be measured by the amount of hospitalisations within 30 days of follow-up in patients treated outside the hospital.

The secondary outcomes are the safety of the care pathway (30-day mortality and occurrence of complications (readmissions, delirium, falls) within 30 days); satisfaction, usability and acceptance of the care pathway (30-day satisfaction questionnaires (patients, informal caregivers and treating physicians) and semi-structured in-depth interviews with the first 10 patients and their informal caregivers in the hospital-at-home group (and the treating GPs), nursing home group and control group after 2–3 weeks); total number of days of bedridden status or hospitalisation; sleep quantity in the first 2 days after inclusion and on the 7th day as assessed by the core Consensus Sleep Diary; sleep quality, functional outcomes and QoL.^25^ Sleep quality will be assessed by the Patient-Reported Outcomes Measurement Information System (PROMIS) Sleep Disturbance short form 8b on day 7 and day 30 after inclusion.^26 27^ Functional outcomes will be measured using KATZ-15 at 30 days, 6 and 12 months.^28–30^ QoL will be assessed using EQ-5D-5L at 30 days, 6 and 12 months.^31 32^ If available, Dutch validated questionnaires are used.

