#### First study visit

A research team member will visit the patient on location (at home, in the nursing home or hospital) on the first workday after the start of the treatment. During this visit, patients (and their representatives if applicable) will be able to ask additional questions about the PIL and the study. If a patient (or representative on behalf of the patient) agrees to participate, written IC will be asked for participation. In case a representative has provided written IC for an incapacitated patient (eg, in case of delirium), and the patient’s medical condition improves over time, the patient will be asked for written IC when the patient is considered competent again. When a patient has given written IC, their informal caregiver and treating physician will also be approached to participate in the study.

During this first visit, baseline information will be collected from the patient. This will include demographic information and a geriatric assessment (GA). A GA is an evidence-based, systematic procedure used to objectively describe the health status of older adults, focusing on somatic, functional and psychosocial domains; and aimed at constructing a multidisciplinary treatment plan. The GA will include the following validated tests: the Charlson Comorbidity Index, G-8 screening tool, 6-item Cognitive Impairment Test, functional status (KATZ-15 and living situation) and QoL (EQ-5D-5L).^34–36^ Ethnicity and religion are included in the demographic information as the area of The Hague has a multicultural society and these factors may influence a patient’s care system and thereby the choice of treatment location. Dementia research has shown that a considerable amount of people with a migration background makes limited use of professional homecare, and needed care is often taken over by family members.^37 38^

During this visit, patients will receive a core Consensus Sleep Diary to fill in on the 2 upcoming days and on the 7th day after inclusion. Patients will also receive a PROMIS Sleep Disturbance short form 8b to fill in on the 7th day after inclusion. The sleep quality/quantity forms will be collected 1 week after inclusion. In the hospital-at-home group, the registration forms will be collected together with the monitoring kits when the patient is released from the care pathway. See Figure 2 and Table 3 for an overview of the time points and collected data.

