### Data analysis plan

The primary outcome is the feasibility of the care pathway. This will be quantitative data. Categorical variables will be presented as counts and frequencies. The quantitative data will be analysed with the Statistical Package for the Social Sciences (SPSS) V.28.

The secondary outcomes will be established by comparing the patients in the care pathway group with the patients in the control group during follow-up. Secondary outcomes are the safety of the care pathway (30-day mortality and occurrence of complications within 30 days); the satisfaction, usability and acceptance of the care pathway; the total number of days of bedridden status or hospitalisation; sleep quantity and quality; functional outcomes and QoL.

Categorical variables will be presented as counts and frequencies. Differences between groups will be tested with χ^2^ tests and multivariate logistic regression models. Continuous data will be presented as means (standard deviations) for normally distributed data or medians (interquartile ranges) for non-normally distributed data. Differences between groups will be tested with independent t-tests or one-way Analysis Of Variance (ANOVA) tests (normal distribution), or Mann-Whitney U or Kruskal-Wallis tests (no normal distribution) depending on the amount of groups to be compared per analysis, and by multivariate linear regression models. All tests of significance will be at two-tailed 0.05 level. The 95% confidence intervals will be used to assess the presence/absence of associations. The quantitative data will be analysed with SPSS V.28.

All recorded interviews will be transcribed by two research team members and hereafter then coded with Atlas.ti V.22. The interview recordings will be saved in a secured folder on the network of the coordinating hospital and will be deleted after verbatim transcription. Transcriptions will be saved on the network of the coordinating hospital. We will apply thematic content analysis to identify and categorise recurrent themes/elements in the interviews. Thereby, we aim to classify the qualitative data in the right sections (implementation, methods, context) of the process evaluation of the implementation of the care pathway.

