Despite its strengths, this study does have some limitations. First, the success of the care pathway partially depends on non-medical issues, such as the availability and capacity of nursing homes and homecare. During the course of this study, these barriers will be evaluated and adjustments will be made if necessary. Another limitation is that the allocation between the care pathway group and the hospital group is based on the time of day and day of the week. Research has shown that illness severity is generally greater outside office hours.^46^ Though, we aim to limit this bias by using limits for oxygen saturation, respiratory rate and maximum of oxygen suppletion in the inclusion criteria, the data of clinical outcomes should therefore be interpreted with caution and be considered explorative rather than proof. Furthermore, it will be challenging to keep all healthcare professionals informed as the care pathway is implemented in an urban area where many healthcare professionals are active. The mixed methods design of the study enables us to get insight in the feasibility, usability and acceptance of the care pathway, although the sample size will be relatively small for measuring effectiveness.

In summary, The Hague RTI Care Bridge will improve our understanding of the possibility and the feasibility to treat patients with an acute moderate-to-severe LRTI or pneumonia outside the hospital. In addition, it will give insight in this new cooperation between two teaching hospitals, the largest GP care group and the two biggest homecare institutions of The Hague, thereby creating possibilities for a similar outpatient treatment for patients with other medical problems (eg, erysipelas and urinary tract infections).

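### For KATZ-15 and EQ-5D-5L the plan lists unadjusted tests beside regression, but neither ties the regression to the day-1 score nor makes it the reported comparison between non-randomised groups

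*Protocol article*

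**What the plan says.** The Data analysis plan of the protocol article sets the comparison for all secondary outcomes: "The secondary outcomes will be established by comparing the patients in the care pathway group with the patients in the control group during follow-up". For continuous data it then states: "Differences between groups will be tested with independent t-tests or one-way Analysis Of Variance (ANOVA) tests". Mann-Whitney U or Kruskal-Wallis tests replace these when the data are not normal. The sentence continues: "depending on the amount of groups to be compared per analysis, and by multivariate linear regression models". All significance tests are two-tailed at 0.05. The section names no covariates for the regression and does not say whether the simple test or the model is the result to be reported.

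The baseline values exist. Under First study visit: "During this first visit, baseline information will be collected from the patient". Table 3 places KATZ-15 and EQ-5D-5L on day 1, at 30 days and at 6 and 12 months. The Outcomes section confirms the follow-up: "Functional outcomes will be measured using KATZ-15 at 30 days, 6 and 12 months". EQ-5D-5L has the same schedule. The first visit falls on the first workday after treatment has begun, in hospital for controls.

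The Discussion describes how the groups arise: "allocation between the care pathway group and the hospital group is based on the time of day and day of the week". It adds: "Research has shown that illness severity is generally greater outside office hours". Its remedy is the set of respiratory and oxygen limits in the inclusion criteria, together with a caution that clinical outcomes are explorative.

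**The concern.** A t-test or rank test on a follow-up score takes the two groups as comparable at the start. Here they are not randomised, and the article itself expects controls to be more severely ill. Function is unlikely to be exempt. The Introduction says that in this illness care at home often falls short because of "increased dependency due to falls, decline in activities in daily living (ADL) or a state of confusion", so dependency bears on where a patient is treated. The inclusion limits concern oxygen saturation, respiratory rate and oxygen need. None of them balances function or quality of life.

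If the groups differ on day 1, part of that difference reappears at follow-up and an unadjusted test reads it as an effect of the pathway. Linear regression on the baseline score would remove the part carried by the measured score and would gain precision in a small study. The article plans regression but fixes neither feature: the baseline term is not named, and the model has no precedence over the simple tests. Two analyses of the same outcome could disagree, with nothing in the article to say which one stands.

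**Working it through.** **The plan's own figure.** The article gives no SD, effect size or power for KATZ-15 or EQ-5D-5L. Its one calculation is the 40 patients for the primary outcome. With 90% (from the 10% readmission rate) against 75%, two-sided 0.05 and 80% power, n = [(1.96 × √(0.90 × 0.10) + 0.8416 × √(0.75 × 0.25)) / 0.15]² = 40.3. The stated 40 is thus reproduced to within rounding (power at 40 is 79.8%). It has no bearing on this point.

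**Inputs.**
- From the article: 50 patients per group (Sample size, described there as ideal); two-tailed 0.05 (Data analysis plan).
- Assumed: correlation r between day-1 and follow-up score of 0.3 to 0.7; day-1 imbalance d of 0.2 to 0.5 SD; equal SDs; no true effect of treatment location; complete follow-up.

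**Formulas.**
- Standard error of the unadjusted difference, in SD units: √(2/50) = 0.20.
- Bias of the unadjusted difference: r × d.
- Rejection rate under a true null (normal approximation): Φ(λ − 1.96) + Φ(−λ − 1.96), with λ = r × d / 0.20.
- Detectable difference at 80% power: (1.96 + 0.8416) × 0.20 = 0.56 SD unadjusted, multiplied by √(1 − r²) when adjusted.

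**Results.**

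| r | d (SD) | Bias (SD) | False-positive rate, unadjusted test | Detectable difference, adjusted (SD) |
|---|---|---|---|---|
| 0.3 | 0.2 | 0.06 | 6.0% | 0.535 |
| 0.3 | 0.5 | 0.15 | 11.7% | 0.535 |
| 0.5 | 0.3 | 0.15 | 11.7% | 0.485 |
| 0.5 | 0.5 | 0.25 | 24.0% | 0.485 |
| 0.7 | 0.3 | 0.21 | 18.3% | 0.40 |
| 0.7 | 0.5 | 0.35 | 41.7% | 0.40 |

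Worst corner: λ = 0.35 / 0.20 = 1.75, so the rate is Φ(−0.21) + Φ(−3.71) = 0.417. Mildest corner: λ = 0.06 / 0.20 = 0.30, so the rate is Φ(−1.66) + Φ(−2.26) = 0.060.

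**Two qualifications.** The adjusted figures ignore the small price of imbalance itself, a factor of √(1 + d²/4). At d = 0.5 this is √1.0625 = 1.03, which turns 0.535 into 0.55 and 0.40 into 0.41; both remain below 0.56. With fewer than 50 per group the bias in SD units does not change. The standard error grows, so the false-positive rates fall and all detectable differences rise.

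**The case against.** The strongest reply is that regression is already planned. A reader who stops at the t-tests might infer that these outcomes are tested only without adjustment, so that baseline differences must pass into the result. The article does not support that: the same sentence adds multivariate linear regression, nothing excludes the baseline score from it, and the instruments are collected on day 1. Nor does the article say whether the simple tests use follow-up scores or changes from baseline, because the sentence is generic for all continuous outcomes. This reply stands. The false-positive rates above describe the unadjusted test and not the plan as a whole.

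A second reply is that covariate lists and the ranking of secondary analyses usually sit in a full protocol or analysis plan, which is not shown. That also stands, so this is not a demonstrated error. What remains is that the article does commit to unadjusted significance tests between groups it expects to differ, and gives the better analysis no precedence.

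Third, the Discussion concedes the confounding and calls the clinical outcomes explorative, and the primary outcome is a one-group percentage that this point does not touch. This limits the importance of the point. It is not a reason to prefer the weaker comparison when the covariate is already in hand.

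Finally, a reader might infer that the day-1 KATZ-15 is an invalid baseline that must be replaced by recalled pre-illness function. The article does not state the reference period of that assessment, so this cannot be concluded. The timing of the visit is a fair caveat on adjustment and nothing more.

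**Conclusion.** The point holds as an improvement available at no cost. For KATZ-15 and EQ-5D-5L at three follow-up times, the article puts unadjusted 0.05-level tests and an unspecified regression side by side, in groups whose comparability it doubts. Under the assumed ranges (50 per group, correlation 0.3 to 0.7, imbalance 0.2 to 0.5 SD) the unadjusted comparison is biased by 0.06 to 0.35 SD and rejects a true null about 6% to 42% of the time. The lower end is close to nominal and the upper end is serious; the article offers nothing to say where in the range this study lies. Baseline adjustment removes the bias carried by the measured score and takes the detectable difference from 0.56 SD to between 0.535 and 0.40 SD.

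Adjustment does not make the comparison causal. The day-1 score is taken after treatment has begun and in hospital for controls. A control admitted on a Friday evening might first be seen on Monday; some pathway patients who start on a Friday or at the weekend would wait as well. If early treatment location already affects the score, adjusting for it is incomplete. Unmeasured severity also remains.

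**What to change.** Add to the Data analysis plan: for KATZ-15 and EQ-5D-5L at 30 days, 6 and 12 months, the reported between-group comparison is the linear regression of the follow-up score on group and the day-1 score of the same instrument, given as an adjusted difference with its 95% confidence interval. The t-tests, ANOVA and rank tests on these outcomes are descriptive.

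Add to the limitations: the day-1 score is recorded on the first workday after treatment starts, in hospital for controls, so adjustment may be incomplete and the comparison remains explorative.

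The cost is a few sentences. The data, visits and software are already planned, and no extra patients are needed.

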### Sample size

Ideally, 50 patients will be treated outside the hospital (care pathway group) and 50 patients will be treated in the hospital (control group). A power analysis was performed for the evaluation of the feasibility of the care pathway. In clinical practice, approximately 10% of the hospitalised patients are readmitted to the hospital after discharge. Our hypothesis is that in at least 75% of the older adults with an acute LRTI or pneumonia who are treated outside the hospital (at home or in a nursing home) according to the care pathway (care pathway group), hospitalisation can be avoided (complete treatment outside the hospital during 30-day follow-up). An 80% power with an alpha of 0.05 for an one-sample study will be achieved if 40 patients are recruited for the care pathway group.

For the qualitative endpoints, data collection (interviews) will be performed until data saturation is reached. When a patient is included and his/her informal caregiver and/or treating physician does not want to participate or cannot participate in the study, the patient will remain in the study and no extra patient will be included to make up for the missing informal caregiver and/or physician.

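### Sleep diary, PROMIS, KATZ-15 and EQ-5D-5L are measured repeatedly, but every method named for them takes one independent value per patient and none uses the repeats jointly

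*Protocol article*

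**What the plan says.** The Outcomes section and Table 3 fix the schedule:

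- Sleep diary: "sleep quantity in the first 2 days after inclusion and on the 7th day", so three occasions.
- PROMIS Sleep Disturbance: days 7 and 30, so two occasions.
- KATZ-15: "Functional outcomes will be measured using KATZ-15 at 30 days, 6 and 12 months", plus a baseline value at the first study visit.
- EQ-5D-5L: the same three follow-up occasions, plus baseline.

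For continuous data the Data analysis plan states: "Differences between groups will be tested with independent t-tests or one-way Analysis Of Variance (ANOVA) tests (normal distribution". For data that are not normally distributed it names the Mann-Whitney U and Kruskal-Wallis tests. The choice within each pair depends on how many groups are compared, so ANOVA is not there to handle repeated visits. Multivariate linear regression is added, with no covariates given. On the level it says: "All tests of significance will be at two-tailed 0.05 level". It names no mixed model, generalised estimating equations (GEE) or repeated-measures analysis, and no key time point for these four instruments.

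The Discussion treats the clinical outcomes as exploratory because allocation follows time of day and day of the week.

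**The concern.** The list of methods does not match the data the same article schedules. A t-test, one-way ANOVA, rank test or ordinary linear regression expects one independent value per patient, whereas these instruments give two or three correlated values after inclusion. An analyst following the list could:

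- test each time point separately, giving several chances of a false positive per instrument, each test resting on whoever answered at that contact;
- pool the occasions as if they came from different patients, which understates the standard error;
- reduce each patient to one summary value, which is valid with complete data but is not specified.

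With a target of about 50 per group, the study would do well to use the repeated values it already collects, and to say beforehand which contrast is the one to read.

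**Working it through.** **The plan's own figure.** The only sample-size figure concerns the primary outcome: "An 80% power with an alpha of 0.05 for an one-sample study will be achieved if 40 patients are recruited for the care pathway group". Reading the stated rates as 90% versus 75% free of hospitalisation, two-sided 0.05, normal approximation: n = [1.96·√(0.90·0.10) + 0.84·√(0.75·0.25)]² / 0.15² = 40.3. It reproduces to within rounding, but has no bearing here, because the secondary outcomes have no sample-size basis.

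**Inputs.** Occasions after inclusion: 3, 2, 3 and 3 (Outcomes, Table 3). Level: 0.05 two-sided per test (Data analysis plan). Group size: 50 per group (Sample size). The article gives no correlation between occasions (ρ) and no rate of missed contacts, so both are assumptions below, with ρ taken as equal between all occasions.

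**Number of tests.** One group comparison per instrument and occasion: 3 + 2 + 3 + 3 = 11. One contrast per instrument: 4.

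**Chance of at least one false positive.**

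- 11 independent tests: 1 − 0.95¹¹ = 0.431.
- 4 independent tests: 1 − 0.95⁴ = 0.185.
- 11 tests, correlated within each instrument and independent between instruments (simulation): 42%, 39%, 35% and 28% for ρ = 0.3, 0.5, 0.7 and 0.9.

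**Pooling as independent.** For three occasions the true variance is (1 + 2ρ) times the one reported. The true standard error is therefore √(1 + 2ρ) times the reported one: √1.8 = 1.34 at ρ = 0.4 and √2.4 = 1.55 at ρ = 0.7.

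**Variance of an average, relative to one occasion.** Three occasions: (1 + 2ρ)/3. Two occasions: (1 + ρ)/2. Detectable difference at 50 per group and 80% power: 2.80·√(2v/50) SD, where v is the variance factor. A single occasion (v = 1) gives 0.56 SD.

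| ρ | v, three occasions | v, two occasions | Detectable, three | Detectable, two |
|---|---|---|---|---|
| 0.4 | 0.60 | 0.70 | 0.43 SD | 0.47 SD |
| 0.5 | 0.67 | 0.75 | 0.46 SD | 0.49 SD |
| 0.7 | 0.80 | 0.85 | 0.50 SD | 0.52 SD |
| 0.9 | 0.93 | 0.95 | 0.54 SD | 0.55 SD |

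**With baseline adjustment (KATZ-15 and EQ-5D-5L only).** One occasion: v = 1 − ρ². Average of three: v = (1 + 2ρ)/3 − ρ². At ρ = 0.5 these are 0.75 and 0.417 (0.49 and 0.36 SD); at ρ = 0.7 they are 0.51 and 0.31 (0.40 and 0.31 SD). Table 3 shows no baseline value for the sleep diary or PROMIS, so this route is closed for them.

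**Missed last visit.** Suppose a fraction d misses the last visit and earlier visits are complete. A joint model then multiplies the variance of the last-visit contrast by 1 − d·R², where R² is the share of variance explained by the two earlier visits, 2ρ²/(1 + ρ). For d = 0.1 to 0.3 and ρ = 0.5 to 0.7 the reduction is about 3% to 17%. Against a complete-case regression that already adjusts for baseline, it is about 2% to 7%.

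**The case against.** The strongest objection is that this is a journal article, and that the key time point, the combination of repeated values and the handling of missed contacts belong in a fuller document. That stands for missing-data rules and multiplicity, and their absence is not raised here. It does not dispose of the point, because the article does not leave the method open: it names a set of methods, and that set does not fit its own schedule.

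A reader might infer that the plan will run all 11 tests, drop every patient with a missed contact, and use nothing but simple tests. The article says none of this. It does not state that each time point will be tested or how incomplete patients are treated, and it does name linear regression, which could adjust for baseline KATZ-15 or EQ-5D-5L.

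A reader might also infer that a joint model is worth half as many patients again. That holds only for a three-occasion average at ρ = 0.5 (1/0.667 = 1.50). For PROMIS at the same ρ it is 1/0.75 = 1.33, and at ρ = 0.9 the three-occasion figure is 1/0.933 = 1.07. With complete data, a patient's own mean put into the listed t-test reaches the same variance without any mixed model. For a single-visit contrast with complete data and no baseline adjustment, the joint model gives essentially the t-test result.

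Finally, the article already calls the clinical outcomes exploratory and the sample small for effectiveness, which weakens any argument from the overall false-positive rate.

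**Conclusion.** The point holds in a limited form and is a minor, worthwhile improvement. For four repeatedly measured instruments the plan names only methods for single independent values. If these are applied by time point, there are up to 11 tests, with a chance of at least one false positive of about 28% to 43%, against about 19% for four independent tests. If occasions are pooled as independent, the standard errors are too small. Averaging would give a variance of 0.60 to 0.80 (three occasions) or 0.70 to 0.85 (two) times that of one occasion.

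These variance figures rest on an assumed correlation of 0.4 to 0.7, equal between occasions; the gain shrinks as correlation rises. The documents support a mismatch between schedule and named methods. They do not support saying that the plan commits to a faulty analysis.

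**What to change.** In the Data analysis plan, for each of the four instruments:

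- Fit one longitudinal model (mixed model or GEE) with group, time and group-by-time terms, and the baseline score for KATZ-15 and EQ-5D-5L. Use robust or bootstrap standard errors where scores are skewed, so that the plan's present provision for non-normal data is kept.
- Name one headline contrast in advance. For example, use the average over occasions for the sleep diary and PROMIS, and 30 days for KATZ-15 and EQ-5D-5L. A single average from 30 days to 12 months could hide early harm or late recovery.
- Give the remaining time points from the same model with 95% confidence intervals, as description.
- At 6 and 12 months, use an estimate that conditions on being alive, for example GEE with independence working correlation among survivors, and show mortality beside it. A likelihood-based mixed model implicitly extrapolates scores beyond death, and labelling its result as applying to the living does not change that.

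The cost is slightly more analysis work and no new data. The outcomes stay secondary and exploratory, and the bias from allocating by time of day is not removed.

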**Trial registration number:**

ISRCTN68786381.

STRENGTHS AND LIMITATIONS OF THIS STUDYA major strength of this study is that the care pathway has been co-designed by patients from the start, and their interests were the mainstay in the development of the care pathway.The satisfaction of patients, their informal caregivers and physicians will be evaluated.This study evaluates the real-life application of the care pathway, which ensures that findings can be used immediately to improve the care pathway.The mixed methods design of the study enables us to get insight into the feasibility, usability and acceptance of the care pathway, although the sample size of this study will be relatively small for measuring effectiveness and safety.The success of the care pathway partially depends on non-medical issues, such as the availability and capacity of homecare institutions and nursing homes.

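### The plan lets a 95% confidence interval show the absence of an association without a margin, so an imprecise safety comparison can be read as no difference

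*Protocol article*

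**What the plan says.** All references are to the protocol article.

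- **Data analysis plan, comparison:** "The secondary outcomes will be established by comparing the patients in the care pathway group with the patients in the control group during follow-up". Safety heads the list of these outcomes, as 30-day mortality and complications within 30 days.
- **Data analysis plan, tests:** for categorical outcomes, "Differences between groups will be tested with χ^2^ tests and multivariate logistic regression models". The level is fixed: "All tests of significance will be at two-tailed 0.05 level".
- **Data analysis plan, reading of intervals:** "The 95% confidence intervals will be used to assess the presence/absence of associations".
- **Sample size:** the aim is 50 patients in each group, worded as an ideal. The only power statement concerns feasibility in one group: "An 80% power with an alpha of 0.05 for an one-sample study will be achieved if 40 patients are recruited for the care pathway group".
- **Strengths and limitations list:** "the sample size of this study will be relatively small for measuring effectiveness and safety".
- **Discussion, limitations paragraph:** clinical outcomes are to be read cautiously and as exploratory. The reason given is that illness tends to be more severe outside office hours, when control patients are recruited. The sample is separately called small for measuring effectiveness.

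**The concern.** The interval sentence is an explicit rule of inference, so it is not a detail left to a separate analysis plan. It allows two results, presence or absence. An interval can support absence of a relevant effect only if it lies inside a margin stated in advance, and the article states none. The natural remaining reading is that an interval containing the null value shows absence.

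For common outcomes in a large study this would be loose wording. For death, delirium, falls and readmission with about 50 patients per group, intervals will be wide, and one that includes no effect may also include a serious excess of harm. At stake is whether the report may say that the pathway showed no association with mortality when the data could not settle the matter.

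**Working it through.** **1. The plan's own figure.** The stated 40 patients follow from a one-sample comparison of proportions. The inputs are p0 = 0.10 (readmission rate in Sample size), p1 = 0.25 (the complement of the 75% hypothesis), two-sided alpha 0.05 and power 80%:

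n = [1.960·√(p0(1−p0)) + 0.842·√(p1(1−p1))]² / (p1−p0)²
= [1.960·0.300 + 0.842·0.433]² / 0.15²
= 0.907 / 0.0225 = 40.3.

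This agrees with 40, to rounding. It concerns feasibility in the pathway group only. No comparison between groups was powered.

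**2. Inputs for the safety comparison.** The 50 per group, the chi-square test and the two-sided 0.05 level come from the article. It gives no mortality rate, so control 30-day mortality is an assumption and is varied.

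**3. How often a true doubling would be missed.** For control risk p and pathway risk 2p, the normal approximation with n = 50 per group is

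power = Φ{ [p√n − 1.960·√(2·p̄(1−p̄))] / √[p(1−p) + 2p(1−2p)] }, with p̄ = 1.5p.

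For 10% against 20%: (0.707 − 1.960·0.505) / 0.500 = −0.565, so power is about 29%. Exact enumeration of all possible results with the uncorrected chi-square test gives 30%. The exact figures across the range are:

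| Assumed control mortality | Doubled to | Power | Doubling missed |
|---|---|---|---|
| 3% | 6% | 9% | 91% |
| 5% | 10% | 14% | 86% |
| 10% | 20% | 30% | 70% |
| 15% | 30% | 44% | 56% |
| 20% | 40% | 60% | 40% |

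Power reaches 50% at a control mortality of about 17%. If only 40 per group were recruited, that point would move to about 20%.

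**4. The same check with an interval instead of a test.** The criticised sentence is about intervals, so the rule was also applied to the Newcombe 95% interval for the risk difference. Power is 11% for 5% against 10%, and 27% for 10% against 20%. A doubling would be missed in 89% and 73% of studies, slightly more often than with the test.

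**5. What single results would look like.** The Newcombe interval combines the Wilson limits (l, u) of the two proportions: difference ± √[(distance to one limit)² + (distance to the other)²].

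- *5/50 deaths in each group.* The Wilson limits for 5/50 are 4.3% and 21.4%. The difference is 0, with half-width √[(0.100−0.043)² + (0.214−0.100)²] = 0.127. The 95% interval is −12.7 to +12.7 points.
- *10/50 on the pathway, 5/50 in control.* The Wilson limits for 10/50 are 11.2% and 33.0%. The difference is +10 points. The lower limit is 0.100 − √[(0.200−0.112)² + (0.214−0.100)²] = −0.043, and the upper limit is 0.100 + √[(0.330−0.200)² + (0.100−0.043)²] = 0.242. Twice as many deaths were observed and an excess of 24 points is not excluded, yet the interval includes 0 and could be read as absence.

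**The case against.** The strongest reply is that the sentence is generic. It closes a paragraph covering sleep, quality of life, function and satisfaction as well as safety, and it may mean only that the interval shows whether an association was detected. The authors also disclose the limits themselves: the sample is small, and clinical outcomes are exploratory. Much of this stands, and it lowers the weight of the point. It does not remove it. The caution in the Discussion rests on out-of-hours severity, which is a bias, whereas the problem here is imprecision. Nowhere does the article say that an interval including no effect is inconclusive.

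Three stronger readings are tempting, and the article does not support them.

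- *That the plan commits to declaring the pathway safe.* It does not say so. The Discussion says the results will show whether treatment is feasible, usable and satisfactory, and safety is not in that list.
- *That treating patients outside hospital rests on this comparison.* The primary outcome and the only power calculation concern feasibility. Decisions to continue, adjust or stop lie with a stakeholder group that meets after every five patients treated at home, and no interval rule is mentioned there.
- *That a doubling of mortality would usually be missed, whatever the rate.* This holds only below a control mortality of about 17%. At 20% the test would detect it in about 60% of studies.

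**Conclusion.** The point holds as a fault in the stated rule of inference. With no margin and no inconclusive category, the Data analysis plan permits a conclusion of absence from data that cannot support it, and this reaches the safety outcomes. Its size rests on 50 patients per group and on assumed mortality, with the proportion of missed doublings running from about 91% at 3% control mortality to 40% at 20%. The article's own caveats temper the matter, and the outcomes are secondary and exploratory, so it is minor to moderate.

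**What to change.** Replace the sentence on confidence intervals with: *Group differences will be reported with 95% confidence intervals as a measure of precision; an interval that includes no difference is inconclusive and is not evidence of absence.* For each safety outcome, add that the upper 95% limit of the excess risk will be reported as the harm not excluded, in line with the exploratory status given in the Discussion. The interval method can be left to the analysts; Newcombe's is used here only for illustration.

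The cost is a sentence or two. No patients, data or design change are needed. The downside is that the report can no longer claim that there was no association.
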